### Management, collection, and monitoring of data

All data will be managed at the study center located at the University Hospital Heidelberg, Department of General Practice and Health Services Research. The study center will receive patient data only in pseudonymized form and will not have direct contact with patients (except for interviews with patients who gave their permission to be contacted by the study team). Only authorized staff members are able to enter or edit data. For specific research questions, parts of the data will be made available to partners of the project (University Hospitals Munich and Tübingen) in pseudonymous form after the trial biometrician has finalized the statistical report. The partners guarantee that only the analyzing researchers will have access to the data. It is also planned to make trial data on which scientific publications are based and all the primary data publicly available for re- and meta-analyses after the trial has been completed.

A study nurse will monitor the data entry during the entire study period. Furthermore, the study team will visit all participating practices before randomization to explain organizational issues related to the study. A Data Safety and Monitoring Board (DSMB) consisting of a GP, a statistician, and an expert in spiritual care will be regularly informed about the course of the trial and all safety issues, and asked for advice whether to continue, modify, or stop the trial.

### Sample size

The sample size was calculated using the primary endpoint, the SES6G at T1. With *n* = 22 practices (11 per group) and *n* = 264 (132 per group) patients available for analysis, it will be possible to detect a clinically relevant mean difference of δ = 1 point at T1 between the two treatment groups for the mean SES6G score at a two-sided α of 0.05 with a power of 1 – β = 0.8, assuming a standard deviation of σ = 2.2 based on the results of Lorig et al. [67], a relatively high intraclass correlation coefficient [68] of 0.05, and a cluster size of *m* = 12 (the calculation was done using the function n4means from the R package CRTSize). It is expected that, adjusting for the SES6G score at T0, gender, age, number of comorbidities, and number of medications in the linear mixed model used for statistical analysis will lead to less unexplained variance and thus to an increase in power. Taking drop-out rates of 7.5% at the practice level and 20% at the patient level, respectively, into account, *n* = 24 practices with *n* = 360 patients will be enrolled into the trial. The potential problem of missing values for drop outs will be partly resolved in the primary analysis by application of the pre-defined imputation strategy.

### Statistical methods

The primary objective of this study is to determine the effectiveness of a complex intervention compared with usual care. The primary efficacy endpoint is the SES6G score at T1. The study objective is statistically formulated as a test of the null hypothesis H_0_: μ_I_ = μ_C_ (the mean SES6G score at T1 in the intervention and the control group are equal) against its alternative H_1_: μ_I_ ≠ μ_C_ at a significance level of α = 0.05 (two-sided).

Because of the cluster randomization, the primary efficacy analysis will use a multilevel regression approach with patients at level one and practices at level two. The primary efficacy analysis will be performed by fitting a linear mixed model including the SES6G score at T1 as the dependent variable, treatment group and gender as fixed factors, and SES6G score at T0, age, number of comorbidities, and number of medications as fixed covariates, and practice as a random factor to account for the two-level data structure (patients nested within practices). The results will be presented as the mean between-group difference in SES6G at T1 with the corresponding 95% confidence interval. The associated Cohen’s effect size *d* will be calculated. In addition, the practice-related intracluster correlation coefficient (ICC) will be estimated. The primary analysis will be performed adhering to the intention-to-treat principle. An additional sensitivity analysis will be conducted on the per-protocol analysis set. Missing data for the primary outcome variable will be replaced using multiple imputation [69] which takes the covariates of treatment group, gender, age, number of comorbidities, number of medications, and practice into account by application of the fully conditional specification method [70]. Sensitivity analyses will be performed by applying alternative methods dealing with missing data such as, for example, complete case analysis and best/worst case imputation.

The statistical analyses of the secondary endpoints will use the same multilevel approach as the primary analysis. All statistical tests will be two-sided at the significance level of α = 0.05. Because no adjustments for multiple endpoints are planned, findings will be interpreted with caution in view of the number of statistical tests undertaken. Only the result of the primary efficacy analysis will be interpreted in a confirmatory manner. Confirmatory subgroup analyses are not planned. No interim analysis with regard to efficacy will be done. All analyses will be performed using SAS version 9.4 or higher.

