### Assignment of interventions

As Fig. 2 shows, 360 patients and 24 practices will be recruited (half in the area of Heidelberg, half in the area of Tübingen) and randomized to either intervention or control group using block randomization stratified by region (Heidelberg/Tübingen) to ensure an equal number of intervention and control practices per region. The randomization list will be created by the trial statistician. Since the intervention involves training of GPs and informed consent of patients, blinding of participants is not possible. However, acknowledged measures to reduce bias such as computerized randomization and blinding of outcome assessment will be undertaken.

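### Practices are randomized within region, but region is not among the listed terms of the primary model; a regional difference left after the covariates would, in expectation, make the standard error too large

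*Protocol article*

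**What the plan says.** Under Assignment of interventions, the protocol article allocates 24 practices, half in each area, by "block randomization stratified by region (Heidelberg/Tübingen) to ensure an equal number of intervention and control practices per region".

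Under Statistical methods, the primary analysis is a linear mixed model for SES6G at T1 with "treatment group and gender as fixed factors, and SES6G score at T0, age, number of comorbidities, and number of medications as fixed covariates" and a random effect for practice. The Sample size section names the same adjustment set: "adjusting for the SES6G score at T0, gender, age, number of comorbidities, and number of medications in the linear mixed model". Neither list contains region, and no section adds it elsewhere or gives a reason for leaving it out.

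For the other outcomes the article says "The statistical analyses of the secondary endpoints will use the same multilevel approach as the primary analysis". The multiple imputation "takes the covariates of treatment group, gender, age, number of comorbidities, number of medications, and practice into account"; region is not named there, but practice is, and each practice lies in one region.

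**The concern.** Stratifying by region keeps any regional difference in outcome out of the treatment contrast, because each arm has the same number of practices in each region. A model without region does not know this. It treats the regional difference as unexplained variation between practices, and a random practice effect does not remove that variation; it is where the variation ends up. The model's standard error then describes a less efficient design than the one that was run.

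This is a stated choice and not a detail left open: the terms are listed one by one for the only analysis that the article will interpret in a confirmatory manner. With 22 practices in the analysis, between-practice variance weighs heavily on precision, and the planned power of 0.80 leaves little margin.

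**Working it through.** **Inputs (Sample size section).** "clinically relevant mean difference of δ = 1 point at T1", "two-sided α of 0.05 with a power of 1 – β = 0.8", SD 2.2, ICC 0.05, 12 analysed patients per practice, 11 practices per arm. Enrolment is 24 practices and 360 patients, after losses of 7.5% of practices and 20% of patients. The regional gap D, meaning the difference in mean T1 SES6G left after the listed covariates, is not given. It is varied here from 0 to 1 point as an assumption.

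**Reproducing the plan.**
- Total variance 2.2² = 4.84; between practices 0.05 × 4.84 = 0.242; within practices 4.598.
- Variance of a practice mean: 0.242 + 4.598/12 = 0.6252.
- SE of the treatment difference: √(2 × 0.6252/11) = 0.337.
- Noncentral t power with 20 df at a difference of 1 point: 0.805. Ten practices per arm give 0.763, so 11 is the smallest number that suffices.
- Losses: 22/0.925 = 23.8, so 24 practices; 12/0.8 = 15 patients per practice; 24 × 15 = 360.

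The planned sample size is reproduced.

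**Effect of leaving region out, with the gap added to the planned ICC and no covariate gain.** A gap D balanced over the arms leaves the true variance of the treatment contrast unchanged. With N = 22 practices it raises the expected between-practice mean square by (N × D²/4)/(N − 2) = 0.275 × D². The model SE is taken as √(2 × (0.6252 + 0.275 D²)/11), against a true SE of 0.337. Power and type I error follow from a contrast with the true SE, divided by the SE from the inflated mean square on 20 df.

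| Gap D (points) | Model SE without region | Overstatement | Power without region | Type I error without region |
|---|---|---|---|---|
| 0 | 0.337 | 0% | 0.81 | 0.050 |
| 0.25 | 0.342 | 1.4% | 0.80 | 0.047 |
| 0.5 | 0.355 | 5.4% | 0.77 | 0.040 |
| 0.75 | 0.377 | 11.7% | 0.73 | 0.030 |
| 1.0 | 0.405 | 20% | 0.68 | 0.020 |

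With region in the model, the SE stays at 0.337, power at about 0.80 and type I error at about 0.05 at every gap.

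**The alternative assumption: the gap is part of the planned ICC.** Let region account for a share f of the between-practice variance, so that D = 2√(f × 0.242). With region in the model, the SE is √(2 × (0.242(1 − f) + 4.598/12)/11), on 19 df.
- f = 25%: D = 0.49 points, SE 0.320, power 0.84. The SE of 0.337 without region is 5% too large.
- f = 50%: D = 0.70 points, SE 0.303, power 0.88. The SE without region is 11% too large.
- f = 0: SE unchanged; power goes from 0.805 (20 df) to 0.803 (19 df).

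**Check with the mixed model itself.** REML fits were simulated, 2,500 runs per gap. Twelve practices per region were split 6/6 between the arms, two practices were lost at random, and each of the 15 patients per practice was retained with probability 0.8. A baseline correlation of 0.5 was assumed. At gaps of 0.25, 0.5 and 1.0 points, the mean model SE over the empirical SD of the estimate was 1.03, 1.07 and 1.22 without region, against 1.01 with it. Power was 0.865, 0.844 and 0.754 without region, against 0.872 with it.

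**The case against.** The strongest case on the other side is that the harm may be nil and cannot produce a false claim of benefit. Several parts of it stand.

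- A reader might infer that the SE is overstated whenever the two regions differ. The plan does not support that. A difference already carried by T0 SES6G or the other covariates does no harm. The effect also holds only in expectation: in the simulation, the fit without region gave the smaller or equal SE in about 57% of runs at a gap of 0.25 points, 28% at 0.5 and 1.5% at 1.0.
- A residual gap of 0.5 points or more is half or more of the trial's own relevant difference, between two areas of one federal state. It may not occur.
- A reader might infer that adding region raises power to 0.84 or 0.88. That holds only if the gap is already part of the ICC of 0.05. If it comes on top, region merely keeps power at about 0.80.
- Baseline adjustment, which the article expects to increase power, gives some cushion. Under the assumed correlation of 0.5, power without region was still 0.844 at a gap of 0.5 points.
- The reported practice ICC would absorb a gap (0.05 becomes about 0.06 at 0.5 points and 0.10 at 1.0), but an ICC not conditioned on region is a legitimate quantity and not an error.
- For the secondary endpoints the article promises the same multilevel approach, not the same covariate list. That the omission carries over is an inference.
- Practice is already in the imputation model. If it enters as fixed indicators, region is determined and naming it adds nothing.

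None of this supplies a reason to omit the stratification factor. It limits the size of the point and not its direction.

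**Conclusion.** The point holds in limited form. The listed primary model does not match the stratified design. If a regional difference in T1 SES6G remains after the covariates, the SE is too large in expectation, the interval too wide and the test conservative. Whether such a difference exists cannot be judged from the article. The loss is negligible up to about 0.25 points, a few points of power at 0.5, and serious only near 1 point. These sizes rest on the plan's SD, ICC and cluster size, on an assumed gap and, for the power figures, on whether that gap comes on top of the planned ICC or is part of it.

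It would be wrong to read this as a threat to validity. The treatment estimate is not biased, and type I error is at or below its nominal level. The case for change is that the possible loss is avoidable at almost no cost.

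**What to change.** Add region (Heidelberg/Tübingen) as a fixed factor to the primary mixed model, and to the secondary-endpoint models that follow the same approach, before the data are analysed. In the imputation model, add region only if practice does not already enter as fixed indicators. State the amended term list wherever the adjustment set is named, including the Sample size section.

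The cost is one model term and one cluster-level degree of freedom. If the regions do not differ at all, that is about 0.002 of power. The sample size need not change.

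### The imputation model for missing T1 SES6G leaves out the T0 score that the primary model adjusts for; this costs precision, and biases the group difference if baseline-dependent dropout differs between arms

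*Protocol article*

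**What the plan says.** Under Statistical methods, the primary analysis is a linear mixed model for SES6G at T1. Treatment group and gender are fixed factors, practice is a random factor, and the covariates are "SES6G score at T0, age, number of comorbidities, and number of medications as fixed covariates".

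The same section replaces missing values of the primary outcome by multiple imputation with fully conditional specification, "which takes the covariates of treatment group, gender, age, number of comorbidities, number of medications, and practice into account". Set against the analysis model, this list is complete except for SES6G at T0. No other section adds it.

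Under Sample size, the article plans for loss: "Taking drop-out rates of 7.5% at the practice level and 20% at the patient level". It describes the imputation as pre-specified for the primary analysis and expects it to resolve part of the dropout problem. It also expects adjustment for T0 and the other covariates to reduce residual variance and raise power. Complete case analysis and best/worst case imputation are named as sensitivity analyses. Only the primary efficacy result is to be interpreted as confirmatory.

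**The concern.** An imputation model should contain at least the terms of the analysis model that will be fitted to the completed data. Here the omitted term is the same scale measured on the same patient at baseline. Two consequences follow.

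- **Precision.** An imputed T1 value is tied to the patient's T0 value only through the weak information in gender, age, comorbidities, medications and practice. The analysis then estimates a T0 slope that is too shallow, and part of the gain expected from baseline adjustment is lost.
- **Bias, under a condition.** If patients with low T0 leave more often, their imputed T1 values are drawn as if they resembled completers, and so are too high. If this happens to the same extent in both arms, the shift cancels in the group difference. If the extent differs between arms, it does not cancel. Differential dropout is possible in this trial, because treatment is open and only the intervention arm has the prolonged session and the diary.

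The single confirmatory result depends on this model.

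**Working it through.** **Inputs from the article (Sample size).** Test and power: "at a two-sided α of 0.05 with a power of 1 – β = 0.8". Effect: "clinically relevant mean difference of δ = 1 point at T1". SD: "assuming a standard deviation of σ = 2.2". ICC: "a relatively high intraclass correlation coefficient [68] of 0.05". Analysed cluster size: "a cluster size of *m* = 12". Dropout is 7.5% of practices and 20% of patients.

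**Inputs assumed, because the article gives none.** The T0–T1 correlation r is set to 0.5 and 0.7. Dropout is about 20% per arm (in one scenario 10% control, 30% intervention). Its log-odds change by 0 or 0.8 in size per SD of T0.

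**Step 1: the plan's own figure.** Individually randomised, 76 patients per arm are needed. The design effect is 1 + (12 − 1) × 0.05 = 1.55, and 76 × 1.55 = 117.8 per arm, or 9.8 practices. With the t distribution on 2k − 2 df for k practices per arm, power is 0.763 for 10 per arm and 0.805 for 11. This gives 22 practices and 22 × 12 = 264 patients, as stated. Inflation: 22/0.925 = 23.8, so 24 practices; 12/0.8 = 15 patients each; 24 × 15 = 360. The sample size reproduces and is not affected by this point.

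**Step 2: attenuation.** If a share f of T1 values is unrelated to T0, the fitted slope is about (1 − f) times the true slope. With f = 0.20: 0.80 × 0.50 = 0.40 and 0.80 × 0.70 = 0.56.

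**Step 3: bias in the group difference.** Let g be the mean T0 of completers minus that of dropouts, in points. The arm mean is shifted upwards by about f × r × g, so

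bias ≈ r × (f_I × g_I − f_C × g_C).

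This is zero when rate and dependence are equal in the two arms. With a log-odds slope of −0.8 per SD and about 20% dropout, numerical integration over a normal T0 with SD 2.2 gives g = 1.60. For dependence in the intervention arm only, bias ≈ 0.5 × 0.202 × 1.60 = 0.16 at r = 0.5, and 0.7 × 0.202 × 1.60 = 0.23 at r = 0.7.

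**Step 4: simulation.** The settings were 22 practices of 15 patients, SD 2.2, ICC 0.05, true difference 1, 10 imputations, a random-intercept analysis adjusted for T0, Rubin's rules, t with 20 df, and 600 runs per scenario. The other covariates were treated as non-prognostic. The Monte Carlo SE of a mean estimate is about 0.01.

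| Dropout scenario | Bias without T0, r = 0.5 / 0.7 | Bias with T0 | Power without T0 | Power with T0 |
|---|---|---|---|---|
| Completely at random, 20% | −0.002 / +0.016 | +0.001 / +0.017 | 0.808 / 0.912 | 0.845 / 0.950 |
| Depends on T0, same in both arms | +0.005 / +0.012 | +0.009 / +0.013 | 0.805 / 0.907 | 0.833 / 0.962 |
| Depends on T0 in intervention arm only | +0.166 / +0.223 | +0.010 / +0.007 | – | – |
| Same dependence, 10% vs 30% missing | +0.139 / +0.191 | −0.005 / −0.012 | – | – |
| Opposite dependence in the two arms | +0.308 / +0.447 | −0.004 / +0.017 | – | – |

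Power is not shown where the estimate is biased, since the rejection rate then reflects the bias. In the first two rows the loss is 2.8 to 5.5 percentage points. In the first row the mean standard error is 0.348 without T0 against 0.328 with it (r = 0.5), and 0.317 against 0.273 (r = 0.7). The T0 slope there is 0.397 and 0.561, matching Step 2. The complete case analysis with T0 in the model has bias of at most 0.017 in every row.

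**Limit of the simulation.** Practice entered the imputation as separate effects. In the first row the multiple-imputation standard errors exceed the empirical spread (at r = 0.5, 0.348 against 0.295 without T0, and 0.328 against 0.292 with it). The comparison between the two models is therefore more reliable than the absolute power levels.

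**The case against.** The strongest counter-arguments are these.

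- **Baseline-dependent dropout need not bias the comparison.** This stands. A reader might infer that any dependence of dropout on baseline self-efficacy biases the primary result. The second row of the table shows otherwise: with the same rate and dependence in both arms the shift cancels. The article predicts no differential dropout.
- **The bias figures rest on chosen scenarios.** This stands. Neither the T0–T1 correlation nor the dropout mechanism is given, and opposite dependence in the two arms is an extreme case. The figures show what could happen and do not forecast it.
- **The power loss does not break the design.** This stands. The 0.80 target was reached without baseline adjustment, and simulated power without T0 in the imputation is 0.805 or more in the unbiased scenarios.
- **A safeguard is already planned.** This stands in part. A complete case analysis using the T0-adjusted model would be nearly unbiased here and would reveal a distortion. It is a sensitivity analysis, however, and if the two disagreed the plan would still draw its confirmatory conclusion from the imputed result.
- **T0 and T1 might be imputed jointly.** Fully conditional specification allows this, and T0 would then predict T1 implicitly. But the article sets the primary endpoint at T1 and lists the imputation covariates explicitly, so the wording would still need correction.

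Two further inferences are tempting but not supported. One is that patients with a missing T0 score drop out of the primary analysis; the article does not say how missing baseline values are handled, and that is commonly left to the analysis plan. The other is that 1 − 264/360 = 26.7% of outcomes would be imputed with T0 available but unused. That share includes the loss of whole practices; expected patient-level dropout is 20%.

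**Conclusion.** The point holds in a limited form. As written, the imputation model does not match the primary analysis model, because it omits SES6G at T0.

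The loss of precision needs no differential dropout. It amounts to about 3 to 5 power points at 20% patient dropout for assumed correlations of 0.5 to 0.7, with power remaining at or above the planned 0.80. Bias in the group difference is conditional: about 0.14 to 0.45 points against a target of 1 where baseline-dependent dropout differs between arms in rate or form, and none where it is the same. Its sign depends on who leaves; in the scenarios shown the intervention looks better than it is. The mismatch itself follows from the text alone, whereas every size quoted depends on the assumed correlation and dropout mechanism.

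**What to change.** Add SES6G at T0 to the variables of the fully conditional specification imputation model, and state that this model contains every term of the primary mixed model. If joint imputation of T0 and T1 was intended, say so explicitly. Keep the complete case analysis with T0 adjustment as a sensitivity analysis.

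The cost is one variable in the wording of the protocol or analysis plan, settled before the data are analysed. T0 is already collected, so no new data and no more patients are needed, and the sample size is unchanged.

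### The T1 imputation model leaves out baseline SES6G and does not say practice is random; with practice as a class covariate, lost practices are inestimable and the standard error is about 10–15% too large

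*Protocol article*

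**What the plan says.** The Statistical methods section replaces missing T1 values of the primary outcome by multiple imputation. The named covariates are treatment group, gender, age, number of comorbidities, and "number of medications, and practice into account by application of the fully conditional specification method". The analysis model in the same paragraph differs in two ways. It adjusts for SES6G at T0, and it takes "practice as a random factor to account for the two-level data structure". The analysis follows intention to treat. Complete-case and best/worst-case analyses are named as sensitivity analyses. On software the section says only: "All analyses will be performed using SAS version 9.4 or higher".

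The Sample size section plans for losses at both levels ("Taking drop-out rates of 7.5% at the practice level and 20% at the patient level") and expects the imputation to deal partly with the resulting missing values. It also expects adjustment for T0 and the other covariates to add power.

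**The concern.** An imputation model should carry at least the variables and the clustering of the analysis model. This list does not carry the baseline score, and it leaves open how practice enters.

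- **Baseline.** T1 values drawn without T0 have no relation to T0 beyond what the other covariates carry. The completed data then show a weaker T0–T1 relation than the real one, and part of the expected precision is lost. This holds however practice is handled.
- **Practice.** Practices are the randomized units, so each lies wholly in one arm. If practice is a class covariate, treatment adds nothing to the model. A practice with no T1 data has no estimable effect. The imputed values also carry more between-practice spread than the random-intercept analysis assumes.

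At stake are the estimate and interval for the one result that the plan reads as confirmatory, and the ICC it intends to report.

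**Working it through.** **Inputs from the Sample size section:** 24 practices and 360 patients enrolled (15 per practice), 12 analysed per practice, "assuming a standard deviation of σ = 2.2", ICC 0.05, "clinically relevant mean difference of δ = 1 point at T1", "two-sided α of 0.05 with a power of 1 – β = 0.8", and drop-out of 7.5% (practices) and 20% (patients). **Assumed, not in the document:** values missing at random, and a T0–T1 correlation of 0.6 where baseline is modelled.

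**1. The plan's own figures.** Without clustering, 76 per arm. Design effect 1 + 11 x 0.05 = 1.55, giving 117.8 per arm, or 117.8/12 = 9.81 practices. With t quantiles this becomes 10.85, so 11 practices per arm, 264 patients, power 0.805. Inflation: 22/0.925 = 23.8, so 24; 12/0.8 = 15; 24 x 15 = 360. The sample size reproduces and is not in question.

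**2. Lost practices.** 24 x 0.075 = 1.8 practices; 1.8 x 15 = 27 patients of 360.

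**3. Aliasing, with practice as class covariate.** Intercept + treatment + 23 practice indicators = 25 columns of rank 24. Without treatment the rank is still 24. With two practices lost, the rank on observed rows is 22, so their effects are not estimable. In one simulated data set with observed arm means near 5.7, the fitted mean of a lost practice ran from 5.0 to 6.9 over 200 practice label orders under reference coding, and from about -10 to 33 under effect coding.

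**4. Standard error by hand, no practice lost, no covariates, 3 of 15 patients missing per practice, 10 imputations.**
- Total variance 2.2² = 4.84; between practices 0.05 x 4.84 = 0.242; within 4.598.
- Imputation noise in a practice mean: (3/15)² x (4.598/12 + 4.598/3) = 0.0766.
- Variance of completed practice means: 0.242 + 4.598/12 + 0.0766 = 0.7018.
- Within-imputation variance of the difference: (2/12) x 0.7018 = 0.1170. Between-imputation variance: (2/12) x 0.0766 = 0.0128.
- Reported SE: √(0.1170 + 1.1 x 0.0128) = 0.362.
- True SD: √((2/12) x (0.242 + 0.3832) + 0.0128/10) = 0.325. Ratio 1.11.
- Implied ICC: between-practice variance 0.7018 − 4.598/15 = 0.395, and 0.395/(0.395 + 4.598) = 0.079.

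**5. Simulation of the same case** (ICC 0.05, 400 trials, 10 imputations, no covariates; two lost means one per arm).

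| Practice in imputation | Lost | Mean SE / empirical SD | Ratio | Type I | Power |
|---|---|---|---|---|---|
| Class covariate | 0 | 0.363 / 0.324 | 1.12 | 0.025 | 0.78 |
| Random | 0 | 0.322 / 0.321 | 1.00 | 0.045 | 0.83 |
| Omitted | 0 | 0.302 / 0.325 | 0.93 | 0.048 | 0.855 |
| Complete case | 0 | 0.318 / 0.323 | 0.99 | 0.045 | 0.84 |
| Class covariate | 2 | 0.387 / 0.356 | 1.09 | 0.022 | 0.68 |
| Random | 2 | 0.340 / 0.338 | 1.01 | 0.025 | 0.785 |
| Omitted | 2 | 0.311 / 0.342 | 0.91 | 0.050 | 0.83 |
| Complete case | 2 | 0.332 / 0.340 | 0.98 | 0.043 | 0.82 |

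With none lost, the mean estimated ICC was 0.079 for the class covariate and 0.048 for random practice. Over ICC 0.01 to 0.10 the class-covariate ratio was 1.05 to 1.14. Monte Carlo error is about 0.01 on type I error, 0.02 on power and 3–4% on ratios.

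**6. Baseline omitted.** The observed share is 0.925 x 0.8 = 0.74. If the other covariates carry nothing of T0, a correlation of 0.6 becomes 0.74 x 0.6 = 0.444 in the completed data. Variance explained by T0 falls from 0.36 to 0.444² = 0.20.

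Two simulations with covariates and one practice lost per arm:
- First (300–350 trials, 20 imputations): mean SE 0.350 with practice indicators, 0.313 with a random intercept and the same covariates, 0.273 once T0 is added. Power 0.79, 0.87, 0.94. The steps are 0.037 for practice and 0.040 for T0. With correlation 0.4, both changes together move power from 0.72 to 0.85.
- Second (250 trials): with indicators, the SE is about 16% too large (about 10% with none lost). Power is 0.70 (0.82 with none lost), against 0.84 (0.90) for a random intercept plus T0.

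Absolute power differs between these runs, so only contrasts within a run should be read.

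**7. Attenuation.** If treatment is the redundant column dropped and one practice per arm is lost, one of 12 practices in one arm is filled at the other arm's level: 1 − 1/12 = 0.917. The two simulations gave 0.92 and about 0.90.

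**The case against.** The strongest reply is that the document never calls the imputation single-level or practice a fixed effect. The same paragraph describes a multilevel analysis, the software sentence names no procedure, and a two-level FCS with a random practice term fits the wording. A condensed article may leave that detail to the analysis plan. This stands: the practice part of the point is conditional, and a reader who infers that the plan prescribes fixed practice effects goes beyond the text.

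Four further limits also stand:
- The SE error is conservative. The document gives no ground for inferring inflated false positives.
- Aliasing alone changes nothing for practices with some T1 data. Only wholly lost practices get arbitrary values.
- Treatment is listed first and practice last. Taken in that order, a practice column goes and treatment stays, so attenuation is not the expected result.
- The trial is sized on observed patients ("With *n* = 22 practices (11 per group) and *n* = 264 (132 per group) patients available for analysis"), and the complete-case sensitivity analysis would help expose an artefact of the imputed practices.

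A reader might also take the first covariate simulation, with SE 0.350 against a true SD of 0.286, to mean that practice coding inflates the SE by 22%. That figure mixes practice coding with the missing baseline.

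The reply does not answer the baseline omission. The covariates are listed one by one, the analysis model's baseline score is not among them, and no reading of practice restores it. Nor is this mere silence: the list is stated, and the plan relies on it for drop-outs.

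**Conclusion.** The point holds in two parts. Unconditionally, the stated imputation list omits SES6G at T0, which the analysis model uses. The loss depends on the T0–T1 correlation; at an assumed 0.6, adding T0 to a random-intercept imputation lowered the mean SE from 0.313 to 0.273. Conditionally, if practice enters as a class covariate, about two practices have no estimable imputation and the SE is about 10–15% too large at ICC 0.05 (9–16% across the calculations). In the covariate-free simulation this costs about 5 points of power with no practice lost and about 10 with two lost, and the estimated ICC is too high. Bias toward zero of about 1/12 needs the further condition that treatment is the column dropped. The point should be settled before analysis. It does not threaten the type I error or the sample size.

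**What to change.** Add SES6G at T0 to the imputation model. State that the imputation is two-level, with a random intercept for practice and treatment as a fixed effect. State also that practices with no T1 data draw their intercept from the between-practice distribution, around their own arm's mean. Dropping practice from the imputation is not a remedy, since the SE is then too small (ratio 0.93 with none lost, 0.91 with two).

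If a two-level imputation cannot be run in the chosen software, make the mixed model on observed T1 values, with T0 as covariate, the primary analysis and keep imputation as a sensitivity analysis. In the covariate-free simulation the complete-case SE was close to correct (ratio 0.99 and 0.98).

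The cost is a few lines of text and modest programming, possibly with the SAS sentence relaxed for this one step. No change to design, data collection or sample size is needed.
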